#### Data collection

Information will be collected at the following times:

Trial entry (from clinical notes)

At 5 weeks post-embryo transfer – following a fetal ultrasound scan to determine viability of the pregnancy and uterine artery Doppler parameters (from clinical notes).

At 10 weeks post-embryo transfer – following fetal ultrasound scan to determine the viability of the pregnancy and uterine artery Doppler parameters (from clinical notes).

Serum results will be returned in batch form at the end of the trial directly to the case report file.

Antenatal screening results (Each patient is given a standard form with self-addressed stamped envelope at the second ultrasound scan to be completed following antenatal screening). Data will be entered directly to the case report file.

The outcome of the pregnancy will be recorded after delivery. Each patient is given a standard letter which is to be completed after delivery. Data can also be obtained from the reproductive centre database (HFEA requirement). Information regarding delivery will also be recorded in the clinical case notes.

A neonatal assessment will be performed shortly after delivery by a member of the neonatal team in the delivery hospital. Each patient is given a standard form with self-addressed stamped envelope at the second ultrasound scan which is to be returned with the delivery details.

There may be a long-term follow-up of all the live births in the trial.

#### Safety considerations

Before recruitment into the trial women will be assessed in terms of their safety for entering the trial during screening via the trial’s entry form. Women in whom progesterone is contraindicated, such as those with liver dysfunction, or women with conditions which may worsen with fluid retention, such as epilepsy, hypertension, asthma, diabetes, cardiac or renal dysfunction or previous history of venous thrombo-embolism, will be excluded from the trial.

As progesterone is a natural hormone, it is not expected to cause serious adverse events in women carefully selected to avoid contraindications and to minimize.

A serious adverse event (SAE) (may or may not be considered related to the Progesterone/placebo pessaries), which results in death, is life threatening, requires hospitalisation or prolongation of inpatient hospitalisation, or results in persistent of significant disability or incapacity.

A serious adverse reaction (SAR) is any adverse reaction (caused by the progesterone/placebo pessaries) which results in death, is life threatening, requires hospitalization or prolongation of existing inpatient hospitalization, or results in persistent or significant disability or incapacity. Examples that may occur in the DOLS trial are jaundice and anaphylactoid reactions.

A suspected unexpected serious adverse reaction (SUSAR) is an adverse reaction which is both unexpected and serious.

SARs or SUSARs will be recorded and reported using the SAE report form (see Appendix C). In the event of a SUSAR, the form will be completed by the trial investigators and given directly to the R&D Department of the Trust within 24 h. The R&D Department, on behalf of the Sponsor, will inform the Chair of the Data Monitoring Committee (DMC) immediately, and the competent authorities within 7 days if the event is life threatening or 15 days if not.

#### Withdrawals

It is expected that the number of withdrawals will be very low due to the highly motivated nature of our patient population.

The DOLS trial is a pragmatic study, and therefore data should be analyzed as intention-to-treat; in other words, analyzing data according to the group to which women were randomized, whether or not they actually comply with the treatment. Stopping treatment does not constitute withdrawal from the study.

#### Analysis

The analysis of this trial will be by ‘intention-to-treat’; therefore, women will be analyzed by the groups into which they were randomized regardless of what intervention they received.

A two group chi-squared test with a 5% two-sided significance level will have 80% power to detect the difference between a control group proportion 80% and a treatment group proportion 90% (odds ratio of 2.151) when the sample size in each group is 210.

Given that the method of analysis is logistic regression with age as a factor, patients will be stratified into two groups; those less than 37 years of age and those older than or equal to 37 years of age. It is recognized that age is an important variable when discussing success rates in assisted conception. To account for this, stratification was employed to optimize the distribution of patients of all ages. A suitable sample size would be 230 per group.

It is anticipated that the drop-outs would be minimal. We aim to recruit a total of 460 patients but we anticipate randomizing no more than 480 women to achieve.

The statistician will remain blinded to the actual identity of the groups for as much analysis as possible.

#### Primary outcome

The primary outcome (proportion of viable pregnancies) will be summarized with a relative risk and 95% confidence interval. The primary analysis will be logistic regression taking into account the age of the woman (that is, the stratification variable).

If other important prognostic factors are imbalanced between the two groups the robustness of the findings will be investigated by including other covariates in the logistic regression.

Although it is anticipated that withdrawal rates will be low, there may be missing values. A range of clinically plausible scenarios will be used to impute missing values in order to test the robustness of the findings. Details of this will be approved by Data Monitoring Committee (DMC) once the magnitude of the problem is known. The statistician may need to be unblinded for these analyses in order to carry out realistic, conservative analyses.

The effect of compliance (as a suitably coded factor) will be investigated by testing the interaction between treatment group and compliance.

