There is a separate randomization sequence for patients stratified less than 37 years of age and patients older than 37 years of age. The randomization sequences were prepared for the trial by [name] (trial statistician) using random sized blocks (2, 4 and 6) using the statistical package available at http://www.randomization.com . Two randomization lists have been prepared. The first list for enrolled women greater than 37 years of age where all ID prefixes begin with a “1” (total 180, 90 per group) and the second list for patients younger than 37 years old where all the ID numbers begin with a “2” (total 360, 180 per group). Trial investigators are to be kept blind to all randomization sequences.

Patients hospital notes are marked with a sticker labeled “This patient is participating in the DOLS study”.

Patients are informed of the date and time of their subsequent second scan which is to be performed 3 weeks following positive urinary pregnancy test (that is, 5 weeks post-embryo transfer/7 weeks gestation).

The investigators, participants and clinicians are unaware of the treatment assignments. Although treatments are blinded, the head pharmacist and the on-call pharmacist will have access to the randomization codes should the need to break the code arise.

Information on patient characteristics, demographics and treatment are transcribed from the hospital case notes to the case report form.

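### The primary model uses age only as a two-level factor cut at 37; adding age in years would bring a small, nearly free gain

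*Protocol article*

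**What the plan says.** The Analysis section links the method to the design: "Given that the method of analysis is logistic regression with age as a factor, patients will be stratified into two groups", the groups being "those less than 37 years of age and those older than or equal to 37 years of age". It gives the reason: "It is recognized that age is an important variable when discussing success rates in assisted conception". The Primary outcome section then settles the form of the covariate: "The primary analysis will be logistic regression taking into account the age of the woman (that is, the stratification variable".

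The only other route to covariates is this sentence: "If other important prognostic factors are imbalanced between the two groups the robustness of the findings will be investigated by including other covariates". It is conditional on observed imbalance, serves as a robustness check, and concerns factors other than age. The Secondary outcomes section plans analysis of covariance and logistic models that stratify for age in the same way.

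No sentence names age in years as a recorded item. The nearest statement is "Information on patient characteristics, demographics and treatment are transcribed from the hospital case notes to the case report form". The Stimulation protocols section also uses the patient's age in choosing a starting dose, and the Treatment allocation steps require age to select the randomization list.

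**The concern.** A two-level cut is needed to run stratified randomization, but the analysis need not stop there. With the binary term alone, women of 25 and 36 share one fitted age effect, and so do women of 38 and 44. If the chance of a viable pregnancy changes with age inside a band, that information is discarded although the protocol itself calls age important. At stake is a little efficiency in the primary test, and by the same wording in the secondary models. The protocol makes this choice itself, so it is not a detail left to an analysis plan that is not shown.

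**Working it through.** **1. Baseline power.** The protocol's own figure is "A two group chi-squared test with a 5% two-sided significance level will have 80% power" with 210 per group for 80% against 90%. The usual formula gives 199 per group (219 with continuity correction), and 210 per group gives 82.1%. The 210 is therefore not reproduced from the stated rates, but nothing below depends on it. At the planned 230 per group:

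z = (0.10 − 1.96 × √(2 × 0.85 × 0.15 / 230)) / √((0.16 + 0.09) / 230) = (0.10 − 0.06526) / 0.03297 = 1.054, so power is 85.4%.

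**2. Inputs.** From the protocol: 460 women, 80% against 90%, two-sided 5%, cut at 37, and lists of 180 older and 360 younger women (180/540 = 33% older). Assumed, because the protocol gives neither an age distribution nor an age effect:
- Set A: truncated normal age, 23 to 43 years, mean 34.6, SD 4.0, 30% aged 37 or over; odds ratio for loss of viability per 5 years from 1.0 to 2.0, with two non-linear variants.
- Set B: age SD 4.65 years; log-odds slope 0 to 0.15 per year. The top slope is an odds ratio of exp(5 × 0.15) = 2.1 per 5 years.

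**3. Information left inside the bands (set A).** The squared correlation of the binary indicator with age in years is 0.57, so 1 − 0.57 = 43% of the variance in age is unused.

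**4. Chance age difference between arms within a band (set A).** Its SD is about 0.33 years below 37 and 0.27 years from 37 up. Overall: √((0.7 × 0.33)² + (0.3 × 0.27)²) = 0.245 years. The shift in the treatment log odds ratio is slope × difference:
- ln(1.5)/5 × 0.25 = 0.020
- ln(2.0)/5 × 0.5 = 0.069, with a difference of about two SDs

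The standard error of that log odds ratio is about 0.28. In simulation, adding age moved the estimate with an SD of 0.02 to 0.04.

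**5. Power (set A, 4000 trials per scenario, randomization balanced within bands).**

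| Odds ratio per 5 years | Stratum only | Stratum + years | Change (points) |
|---|---|---|---|
| 1.0 | 85.6% | 85.8% | +0.2 |
| 1.3 | 86.2% | 86.4% | +0.2 |
| 1.5 | 86.4% | 86.6% | +0.2 |
| 2.0 | 86.4% | 86.8% | +0.4 |
| 1.5, steeper after 35 | 85.9% | 85.8% | −0.1 |
| 2.0, steeper after 35 | 86.6% | 87.2% | +0.6 |

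The +0.2 in the first row, where age has no effect, shows the size of the simulation noise. Set B (5000 paired trials per slope) gave −0.12, +0.12, +0.50 and +0.54 points at slopes 0, 0.06, 0.10 and 0.15, with paired standard errors of 0.12 to 0.22. A single run at slope 0.15 showed +1.1 points; repetition did not reproduce it, so it is not used.

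**6. Effective sample size.** This is the squared ratio of the Wald z values. At an odds ratio of 2.0 in set A, the mean estimate and standard error are 0.844 and 0.2817 with the stratum only, and 0.856 and 0.2839 with age added. So (3.015 / 2.996)² = 1.013. At 1.5 the same arithmetic gives about 1.003. Across all runs the range is about 0.4% to 2%: 460 × 0.004 = 2 women to 460 × 0.02 = 9 women. The standard error rises slightly; as is usual in logistic regression, the gain comes from a larger conditional estimate.

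**7. Validity.** Type I error was 4.5% to 5.8% for every model. With an age effect of 1.5 or 2.0 and no treatment effect, the mean treatment log odds ratio lay within 0.001 of zero for every model.

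**The case against.** The strongest reply is that nothing is broken. Adjusting for the stratification factor is standard, matches the design and gives a valid test. A covariate term in a randomized trial need not be a correct risk model. The gain is a fraction of a power point, on a base that already exceeds the 80% target. It also rests on an assumed age spread and slope. The protocol's remark on age concerns success rates in general, not viability at 12 weeks once the test is positive. Adding age changes the conditional odds ratio, and recruitment had already ended. All of this stands, and it sets the size of the point.

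What does not follow is that the text needs no comment. The protocol fixes the two-level form itself, and its clause on further covariates does not clearly reach age in years.

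A reader might infer that age imbalance within a band biases the treatment estimate. The documents do not support that. Allocation is random within bands, so any such imbalance is chance, and the standard error already covers it. A reader might also take it as stated that age in years is recorded. That is only inferred from the uses of age listed above.

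**Conclusion.** The point holds as a minor matter of efficiency. The primary model leaves prognostic information within each age band unused. Adding age in years would change power by roughly 0 to 0.6 points and raise effective sample size by about 0.4% to 2%. These figures depend on the assumed age distribution and on odds ratios up to about 2 per 5 years; if age has no effect within bands there is nothing to gain. No gain was calculated for the secondary outcomes. It would be wrong to read this as a defect in validity or a material shortfall in power.

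**What to change.** In the Primary outcome section, name one model: logistic regression with treatment, randomization stratum as allocated, and age in years as a single linear term. Use the same age term in the Secondary outcomes models. Name one functional form only; a choice between linear and spline would leave the primary analysis open. Date the change before unblinding. Because the statistician works with groups coded A and B, it should preferably come before any outcome is compared by code. If the present primary model is kept, the extended model could be a named sensitivity analysis.

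The cost is one more degree of freedom, against about 460 × 0.15 = 69 expected non-viable outcomes, and a slightly different conditional odds ratio. No new data should be needed, provided age in years is confirmed to be on the case report form.

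The stratum also needs one definition. The randomization text reads "There is a separate randomization sequence for patients stratified less than 37 years of age and patients older than 37 years of age", which places women aged exactly 37 in neither list, while the Analysis section puts them in the older group. That is a separate point, but the model should carry the stratum actually used.

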Currently at the Hewitt Centre, approximately 32.5% of women have a positive biochemical pregnancy test 2 weeks after embryo transfer. It is this population that is eligible for trial entry and randomization. Once the patient has confirmed a positive urinary pregnancy test they will be invited to join the trial. Eligibility will be confirmed verbally over the telephone according to the trial entry protocol. The patient will then be asked to sign the consent form that they have with them at home and return it to the Hewitt Centre within 24 h. Once the consent form has been completed by the patient, a trial prescription sheet will be sent to the pharmacy with a stated collection time. The patient can then be randomized and the drugs dispensed according to pharmacy protocol. A blood sample will then be drawn for measurement of baseline hormone levels (progesterone, estradiol, free beta-hCG, pregnancy-associated plasma protein-A (PAPP-A), Activin A, Inhibin A and Inhibin B).

The patient will then be given the drug pack that has been prepared by the pharmacy. This drug pack will contain either the placebo pessaries or the progesterone pessaries. They will continue to take these for a further 8 weeks (in other words, up to 10 weeks post-embryo transfer, which is up to the 12 weeks gestation calculated by the last menstrual period).

Inclusion criteria:

1. Biochemical pregnancy confirmed by urinary pregnancy test. If positive then they will be eligible to enter the trial.

2. Progesterone treatment (2 weeks) completed up to the day of the pregnancy test.

3. Patients treated at Hewitt centre only.

4. Only those patients who have been treated with the long-stimulation protocol.

Exclusion criteria

1. All women who are undergoing frozen embryo transfer.

2. Any women not willing to take part will be excluded.

3. All diabetic, epileptic and hypertensive patients on treatment.

4. Poorly controlled asthmatics having had more than one hospital admission in the last year.

5. Patients with renal and cardiac dysfunction (under the care of nephrologist and cardiologist, respectively).

6. Breast cancer patients.

7. Severe liver impairment/jaundice.

8. Previous history of thromboembolism.

9. Transport centre patients (that is, egg collection outside the main hospital).

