## Discussion

### Measure of outcomes

Primary outcome measure:The primary outcome measure is the proportion of all randomized women that continue successfully to a viable pregnancy (at least one fetus with FHR >100 beats/minute) on transabdominal/transvaginal ultrasound at 10 weeks post-embryo transfer/12 weeks gestation (that is, at the end of 8 weeks supplementary trial treatment). The following clinical estimates are available. The success rate at the biochemical testing stage is approximately 32.5%. Currently, without further progesterone supplementation, 80% of these women will carry on successfully with a viable pregnancy (25.8% of clinical pregnancy rate) whilst 20% of these women will miscarry. We anticipate that an increase of 10% from the biochemical to the clinical pregnancy rate would be clinically important and therefore justify an additional 8 weeks supplementation with progesterone, in other words, a reduction of 10% in the miscarriage rate.

Secondary outcomes:

1. Viable pregnancy (at least one fetus with FHR > 100 beats/minute) on transvaginal ultrasound at 5 weeks post-embryo transfer/7 weeks gestation (that is, at the end of 3 weeks supplementary trial treatment).

2. Relationship of serum markers (estradiol, progesterone, Inhibin A, Inhibin B, Actavin A, free beta-hCG and PAPP-A) taken at 5 and 10 weeks post-embryo transfer with treatment allocation, primary outcome and secondary outcomes.

3. A pelvic Doppler will be performed to determine if the blood velocity in the uterine artery is different in the two groups. This will be performed at 5 and 10 weeks post-embryo transfer.

4. Side effects

A visual analogue score relating to the following side effects will be completed at both 5 weeks and 10 weeks post-embryo transfer: nausea, bloating, vaginal discharge and vaginal irritation.

5. Antenatal Down’s Screening Outcomes

Antenatal Down’s screening results for all patients will be monitored, including individual serum quantification for double, triple, quadruple screening and nuchal translucency.

6. Neonatal outcomes

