#### Secondary outcomes

These will be exploratory analyses producing 95% confidence intervals. They will be unadjusted for multiple analyses. The interpretation will take multiple testing and the consequent likelihood of type I errors into account qualitatively.

Continuous outcomes will be analyzed by analysis of covariance and dichotomous variables by logistic regression. In a similar way to the analysis of the primary outcome, these analyses will stratify for age, and the robustness of findings will be examined by including other potentially important prognostic covariates. A range of plausible values will be imputed for missing values.

Where a large proportion of values are missing (typically >25%) only descriptive statistics will be provided.

If any variables are highly skewed, leading to doubts about the validity of the parametric analyses, non-parametric analyses will be carried out or bootstrapping will be used.

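### The robustness analysis of the primary outcome adds covariates only on chance imbalance, and the trial-entry hormone levels are assigned to no analysis

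*Protocol article*

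**What the plan says.** All references are to the protocol article.

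- **Primary model.** Under Primary outcome in the analysis part: "The primary analysis will be logistic regression taking into account the age of the woman (that is, the stratification variable"). This is unconditional.
- **Other covariates, primary outcome.** The next paragraph of that section reads "If other important prognostic factors are imbalanced between the two groups the robustness of the findings will be investigated by including other covariates". It names neither the factors nor what counts as imbalanced.
- **Other covariates, secondary outcomes.** Under Secondary outcomes, continuous outcomes go to analysis of covariance and "these analyses will stratify for age". The same sentence goes on to a robustness check with further prognostic covariates, without an imbalance condition, although it presents the approach as similar to that for the primary outcome.
- **Entry hormones.** Under Recruitment, after randomization and dispensing: "A blood sample will then be drawn for measurement of baseline hormone levels". The list is progesterone, estradiol, free beta-hCG, PAPP-A, Activin A, Inhibin A and Inhibin B. The woman receives the pack after that.
- **Marker outcomes.** Secondary outcome 2, under Measure of outcomes, studies the same seven markers "taken at 5 and 10 weeks post-embryo transfer with treatment allocation, primary outcome and secondary outcomes". The entry value is not mentioned.
- **Other baseline variables.** Demographics and other clinical variables gives them summary statistics only.

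**The concern.** There are two related weaknesses.

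First, the imbalance trigger. In a randomized trial any baseline difference between arms is due to chance. The reason to adjust is that a covariate predicts the outcome. Under the stated rule, a strong predictor that happens to be balanced is left out, and the set of covariates is unknown until the data have been viewed by group. The Trial statistician section says that the statistician will hold the A/B codes and may be unblinded for the missing-value analyses. A robustness analysis whose covariates are chosen at that stage, from an open list, gives less reassurance than one listed beforehand.

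Second, the entry hormone values. They precede study treatment, so they are legitimate covariates, and the trial already pays for them. The entry value of a marker is the natural covariate for its later value, yet the only adjustment named is age, which the Analysis section defines as two bands. At stake is the precision of the between-group comparison for seven markers at two time points.

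**Working it through.** **1. The plan's own figure.** The Analysis section states: "A two group chi-squared test with a 5% two-sided significance level will have 80% power". Its inputs are 80% viable on placebo against 90% on progesterone, with the odds ratio given as 2.151 and 210 women per arm. It then plans 230 per group.

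For the named test, n = [1.960·√(2·0.85·0.15) + 0.842·√(0.8·0.2 + 0.9·0.1)]² / 0.10² = (0.990 + 0.421)² / 0.01 = 199 per group, or 219 with continuity correction. The stated 210 lies between the two. Power is 82.1% at 210. At 230 it is Φ[(0.10·√230 − 0.990)/0.5] = Φ(1.05) = 85.4%. (Rates of 80% and 90% give an odds ratio of 9/4 = 2.25, not 2.151. That and the 210 are separate matters and do not affect this point.) The design therefore passes its 80% target before any covariate is added.

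**2. What a baseline covariate could add to the primary outcome.** The article gives no prognostic strength for any hormone, so strength is an assumption. Simulation: 4,000 trials per setting, 230 per group, marginal rates held at 80% and 90%, one standard normal covariate, logistic regression with and without it. Simulation error of each power is about 0.6 points.

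| Assumed odds ratio per SD | Power without | Power with | Gain (points) | Conditional treatment odds ratio |
|---|---|---|---|---|
| 1.0 | 85.9% | 85.9% | 0 | 2.25 |
| 1.5 | 85.7% | 86.6% | 0.9 | 2.29 |
| 2.0 | 86.4% | 88.2% | 1.8 | 2.36 |
| 3.0 | 86.0% | 89.8% | 3.8 | 2.55 |

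The comparator here has no covariate. The planned model has the age stratum, so any overlap between age and the marker would reduce these gains. The last column shows that adjustment moves the odds ratio away from 2.25 even though the marginal rates are unchanged.

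**3. What the entry value could add to the marker analyses.** With correlation r between entry and follow-up value within arm and age stratum, covariance adjustment leaves residual variance (1 − r²) and multiplies the standard error by √(1 − r²). The values of r are assumed.

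| r | Variance removed | Standard error multiplied by |
|---|---|---|
| 0 | 0% | 1.00 |
| 0.3 | 9% | √0.91 = 0.95 |
| 0.5 | 25% | √0.75 = 0.87 |
| 0.7 | 49% | √0.51 = 0.71 |

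**4. Sections side by side.** Primary outcome makes the extra covariates depend on imbalance; Secondary outcomes does not. Recruitment collects seven entry values; Measure of outcomes and Secondary outcomes use the same seven markers at weeks 5 and 10 and name age alone.

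**The case against.** The strongest reply is that the primary result is untouched. The model is fixed, the quoted sentence concerns robustness only, and it already limits itself to factors that are important prognostically. The covariates in the secondary robustness check could include the entry hormones, covariance analysis leaves room for them, and exact covariate lists often sit in a statistical analysis plan, which is not shown here. The marker outcomes are declared exploratory.

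Most of this stands, and it limits the point. A reader might infer that covariates enter the primary model only when imbalanced, so that the primary estimate is open to selection. The text does not support that: age is always in the model and nothing else enters it. A reader might also infer that omitting the hormones wastes power. That is not shown either. Assuming an odds ratio of about 4.5 per SD would lift power to about 93%, but nothing in the article supports such a marker, and weak or null markers give almost nothing. Nor does the article single out free beta-hCG, or say that entry values predict viability; secondary outcome 2 concerns weeks 5 and 10.

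What the reply does not remove is that the article states a poor selection rule where it could have stated none. It also states an adjustment for the markers that leaves out their own baseline. Both are things the text says, not only detail left for later.

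**Conclusion.** The point holds in a limited form. The imbalance trigger is a weak basis for the robustness analysis of the primary outcome and differs from the article's own approach to the secondary outcomes. The entry hormone values have no stated use, and the marker analyses name age only.

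The gain for the markers is 25% of residual variance at r = 0.5 and 49% at r = 0.7. Those correlations are assumed, but the relation itself is standard. For the primary outcome the possible gain is about 0 to 4 points of power for odds ratios of 1 to 3 per SD, from about 86%. It should not be presented as a loss the trial suffers. The planned primary estimate, test and confidence interval are not put in doubt.

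**What to change.** - **Secondary outcomes.** State that each week-5 and week-10 marker is analyzed with the trial-entry value of the same marker plus the age stratum. Specify the trial-entry sample, because Recruitment also mentions baseline hormone levels measured after the information evening.
- **Primary outcome.** Delete the imbalance condition. Run the covariate-adjusted robustness analysis whatever the balance, with prognostic covariates listed before unblinding: continuous age, and entry hormone values if the team judges them prognostic.
- **Reporting.** Keep the age-stratified logistic regression as the primary analysis. Beside the adjusted odds ratio, which is conditional on the covariates, give a standardized relative risk or risk difference, so that the shift shown in the last column of the power table is not read as fragility.

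The cost is small. Recruitment is complete and the entry sample is part of the existing schedule, so only analysis text changes. Some entry values will be missing and need a stated handling rule; the article gives no figure for how many. Because the hormones stay out of the primary model, the primary analysis does not come to depend on assay completeness.
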